### Outcome measurements

2.5

#### Primary outcome measures

2.5.1

WC will be used as the primary outcome measure. This index will be assessed on week 0, 2,4,6, 8, and 12.

#### Secondary outcome measures

2.5.2

##### Obesity-related indicators

2.5.2.1

Obesity-related indicators are weight (WG); body mass index (weight/height); body fat percentage (F%); basic metabolism value; hip circumference (HC); and waist-to-hip ratio (WC/hip circumference) measured on week 0, 2,4,6, 8, and 12.

##### Serum biochemical indexs

2.5.2.2

Fasting glucose, fasting insulin, insulin resistance index, uric acid, and blood lipid level which includes total cholesterol, triglyceride, low-density lipoprotein, high-density lipoprotein will be measured on week 0, 8.

##### Blood pressure

2.5.2.3

Blood pressure will be measured on week 0, 8.

##### Conversion score of constitution characteristics

2.5.2.4

The constitution characteristics in the Table of Constitution Classification and Judgment of Traditional Chinese Medicine will be adopted as the criterion of constitution determination. The conversion score of constitution characteristics will be then calculated based on the computational formula: Conversion score= [(original score-number of entries)/(number of entries × 4)] × 100. Measurements will be made on week 0, 8, 12.

##### Measurement of the scale

2.5.2.5

The IWQOL—Lite scale, and Emotional and Psychological Assessment scale will be measured on week 0, 8, 12. The lower the total score, the lighter the clinical symptoms of the patient.

### Study procedure

2.6

Before study commencement, baseline demographic data and clinical characteristics will be recorded. Next, all the participants will complete a general information form, and then written informed consent will be provided to them. Participants who meet the inclusion criteria and exclusion criteria will be enrolled, grouped, and given corresponding interventions. The schedule of enrolments, allocation, and assessments is given in Table 1.

**Table 1 T1:**
[figure not shown]
The schedule of enrolments, allocation, and assessments.

### Sample size calculation

2.7

The participants will be randomly divided into moxibustion combined with characteristic lifestyle intervention of TCM (intervention group), moxibustion combined with lifestyle intervention (intervention group), the lifestyle intervention (control group) in a 2:2:1 allocation ratio. The sample size was calculated based on the primary outcome, which is proposed to be the WC. Statistical Analysis System software (version 9.3)(SAS 9.3 Institute Inc., Cary, NC) was used to calculate the required sample size.

Based on the results of previous studies and related literature reports, sample size required for each individual hypothesis testing was estimated at the 1-sided α level 0.025. With other assumptions, the basis of estimated sample sizes was listed in Table 2. To ensure adequate power for each individual hypothesis testing, a sample size of 135 was required, which consists of 54 subjects in the moxibustion combined with characteristic lifestyle intervention of TCM (intervention group), 54 subjects in the moxibustion combined with lifestyle intervention (intervention group), and 27 subjects in the lifestyle intervention (control group). Anticipating a 10% dropout rate, a total of 150 participants were recruited.

**Table 2 T2:**
[figure not shown]
Sample sizes required for each individual hypothesis testing.

### Randomization and blinding procedures

2.8

Eligible participants will be allocated to the 3 groups in a 2:2:1 ratio by a computer according to the central simple completely random grouping method of the SAS package (SAS statistical software version 9.3; SAS 9.3 Institute Inc., Cary, NC). The random scheme was compiled and produced by random statisticians in the data center of Chinese Academy of Chinese Medical Sciences, and generated through SAS software PROC PLAN process statement. The random number assignment will be generated by an independent statistician who will not be a member of the research team. Eligible subjects who have written an informed consent will be randomly assigned to one of these 3 groups. All the researchers who evaluate the results above will not be aware of which group the participants have been assigned to. All processes will be recorded and saved as appropriate.

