### Study design

2.2

This randomized controlled trial will be conducted at the Department of Acupuncture of five hospitals including Hubei Provincial Hospital of Traditional Chinese Medicine, Shanxi Provincial Hospital of Traditional Chinese Medicine, Shenzhen Bao’an Traditional Chinese Medicine Hospital Group, Wuhan Hospital of Traditional Chinese and Western Medicine, Xiangyang Hospital of Traditional Chinese Medicine from September 2020 to January 2022. The participants recruited from our outpatient departments will be randomly allocated to three groups, these are the intervention group (moxibustion combined with characteristic lifestyle intervention of TCM, n = 60,expected); the other intervention group (moxibustion combined with lifestyle intervention, n = 60,expected) or the control group (lifestyle intervention, n = 30, expected). The participants in the 2two intervention groups will receive 48 sessions of moxibustion treatment over 8 weeks. The characteristic lifestyle intervention of TCM will also last 8 weeks, whereas the lifestyle intervention will last 12 weeks including 8-week treatment period, 4-week follow-up period. The study design is depicted in Figure 1.

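### Central 2:2:1 allocation described as simple and completely random, with no stratification by hospital, leaves balance within the five hospitals to chance and does not say whether arm totals are fixed

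*Protocol article*

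**What the plan says.** Section 2.8 (Randomization and blinding procedures) states that participants are "allocated to the 3 groups in a 2:2:1 ratio by a computer according to the central simple completely random grouping method" and that the scheme was "generated through SAS software PROC PLAN process statement". It mentions neither blocks nor a hospital stratum.

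Section 2.2 (Study design) says the trial is "conducted at the Department of Acupuncture of five hospitals". It gives the arm sizes as 60, 60 and 30 and marks each as expected, for example "the control group (lifestyle intervention, n = 30, expected". Recruitment per hospital is not stated.

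Section 2.7 (Sample size calculation) is firmer: "To ensure adequate power for each individual hypothesis testing, a sample size of 135 was required", made up of 54, 54 and "27 subjects in the lifestyle intervention (control group". It continues: "Anticipating a 10% dropout rate, a total of 150 participants were recruited".

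Section 2.10 (Statistical analysis) names the t test, rank sum test, chi-square test, repeated-measures analysis of variance and MANOVA. It does not mention hospital.

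**The concern.** Two features of the design sit badly with the allocation method that Section 2.8 names.

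- **Arm totals.** Section 2.7 requires 27 evaluable controls for adequate power. The control arm is half the size of each other arm and enters every comparison with lifestyle intervention alone. If each participant is allocated independently, the size of that arm is random.
- **Balance within hospital.** The primary outcome is a tape-measured waist, moxibustion is given by therapists over 48 sessions, and diet and exercise instruction is given at the hospitals. Each of these could plausibly vary between hospitals, although the article does not say that they do. Hospitals of equal size would expect only six controls each, so the mix of arms could differ noticeably from one hospital to the next.

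What would be lost is precision and protection against an unlucky draw. The validity of the comparison is not at risk.

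**Working it through.** **Inputs.** From Sections 2.2, 2.7 and 2.8: N = 150, allocation 2:2:1 (control probability 1/5), 54/54/27 evaluable, 10% dropout, one-sided alpha 0.025, five hospitals. Assumed: 80% design power (effect size, SD and power are in Table 2, not shown), 30 participants per hospital, and centre intraclass correlations (ICC) of 0.05 and 0.10.

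**The plan's own figure.** 135/0.9 = 150, 54/0.9 = 60 and 27/0.9 = 30. The inflation for dropout reproduces. The 135 itself cannot be checked without Table 2.

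**Control arm, literal reading.** The count is Binomial(150, 0.2).
- Mean 30, SD = √(150 × 0.2 × 0.8) = 4.9, central 95% range 21 to 40.
- P(exactly 30) = 8%, P(fewer than 30) = 47%, P(22 or fewer) = 6%.
- P(fewer than 27 evaluable) with 10% random dropout, Binomial(150, 0.18): 47%. For comparison, with exactly 30 randomised, Binomial(30, 0.9): 35%. The method therefore adds about 12 points; dropout alone accounts for the rest.

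**Control arm, permuted-list reading.** If PROC PLAN permuted one list of 60/60/30, the totals are exact once the list is used up, and none of this variation arises.

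**Power, literal reading.** The effect that gives 80% at 54 v 27 is d = (1.96 + 0.84) × √(1/27 + 1/54) = 0.66 by the normal approximation (0.669 with the t distribution).
- At 22 controls randomised, 22 × 0.9 ≈ 20 are evaluable. Power is 71% at 54 v 20. It is 72% if the missing controls go to the other two arms: (135 − 20)/2 = 57.5 each.
- Averaged over the randomisation, power is about 79% (79.1% to 79.4% by simulation) against 80% with fixed sizes.
- If the design power were 90%, the average would be 89.2%.

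**Balance within hospital (30 per hospital assumed).**
- Simple randomisation: P(3 or fewer controls in one hospital) = 0.123 from Binomial(30, 0.2). For at least one of five: 1 − (1 − 0.123)^5 = 48%.
- One permuted list, totals forced to 60/60/30: 44%.
- With assumed sizes of 50/40/30/20/10, the chance that some hospital has no controls is about 11% (simple) or 10% (permuted list).

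The within-hospital result is thus nearly the same on both readings.

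**What a hospital term would gain.** If a share ICC of the outcome variance lies between hospitals, removing it divides the SD by 1/√(1 − ICC), so power becomes Φ(2.80/√(1 − ICC) − 1.96).
- ICC 0.05: Φ(2.874 − 1.96) = 82%.
- ICC 0.10: Φ(2.953 − 1.96) = 84%.

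**Validity.** Under simulated simple 2:2:1 allocation over five hospitals of 30, an unadjusted t test kept its type I error at about 5% for both ICC values.

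**The case against.** The best defence is that simple randomisation is a legitimate method. Allocation does not depend on hospital, chance imbalance is already covered by the error rate of the test, and the expected power loss is about 1 point because draws above 30 controls gain power. All of this stands. A reader might infer that treatment is confounded with hospital; the documents do not support that, since random allocation introduces no systematic link between the two.

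A reader might also infer that the control arm is certainly left unrestricted. Section 2.8 does not settle this. Its wording points that way, and Section 2.2 calls the sizes expected. But the scheme was compiled in advance with PROC PLAN, which can permute one list with fixed totals, and the word simple may only mean unstratified. The range of 21 to 40 applies only to the literal reading.

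A third inference would be that the analysis ignores hospital. No test named in Section 2.10 carries such a term, and the t and rank sum tests cannot. But a hospital covariate is commonly left to the statistical analysis plan, which is not shown, so its absence from the article is not a fault in itself.

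Finally, Sections 2.4.1 and 2.4.2.1 set common diet and exercise targets and one moxibustion regimen, so differences between hospitals are plausible but undocumented. What the defence does not remove is that a list without a hospital stratum cannot secure 2:2:1 within each hospital, on either reading.

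**Conclusion.** The point holds as a cheap improvement and a request for clarification; it is not a flaw that threatens validity. The method named in Section 2.8 does not secure balance within hospital however it is read. Whether the totals of 60/60/30 are secured depends on a detail that the text leaves open.

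The size is modest. On the literal reading, the loss is about 1 point of power on average and about 8 to 9 points at a draw of 22 controls, with a 6% chance of a draw that low or lower. A hospital term could add about 2 to 4 points. These figures rest on an assumed 80% design power and assumed ICCs of 0.05 to 0.10; the within-hospital probabilities rest on assumed hospital sizes.

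**What to change.** - State in Section 2.8 whether each participant is allocated independently or from one permuted list with fixed totals.
- If allocation has not started, have the independent statistician generate the PROC PLAN list as permuted 2:2:1 blocks of sizes 5 and 10 in random order, stratified by hospital and concealed from the sites. N stays 150. Totals land at or close to 60/60/30, with small deviations from incomplete last blocks.
- Include hospital as a fixed effect in the primary waist circumference model.
- If allocation has started, keep the existing list and add only the hospital term. This may well be the case, since Section 2.8 describes the scheme as already compiled.

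The cost is one regenerated list within the existing central system, one model term and four degrees of freedom (5 − 1). Blocking makes allocation slightly more predictable where therapists know the treatment; central allocation and varying block size limit this.

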### Data collection and management

2.9

Clinical observation results such as the demographic data of the participants, clinical information, and any other data related to this study will be documented on case report forms (CRFs). Participants will receive a food and exercise diary and will be asked to complete from baseline to the end of the follow-up period. The diary will be collected every 2 weeks separately from each hospital. A corresponding computer database will be established and the medical records of this clinical trial will be input and stored by researches in a password-protected electronic database, and be kept strictly confidential. A member in the study team who is not involved in these data collection will check the database data and source documents. The hard copies of all the clinical data and CRFs will be stored in a fixed locker.

### Statistical analysis

2.10

The SPSS software v19.0 will be used for statistical processing. The data of all participants will be conducted in the final statistical analysis which will be in accordance with the per-protocol principle and the intent-to-treat principle. Measurement data will be presented in the form of mean ± standard deviation, whereas count data will be expressed as percentage and number.

The homogeneity test of variance and normal distribution test will be adopted for measurement data. Count data and grade data will be described by rate and composition ratio. Student *t* test will be used when the data obey the normal distribution, whereas the data not obeying the normal distribution will use rank sum test. Comparison is performed by *χ*^2^ test, repeated measurement data are expressed by mean ± standard deviation and intra-group comparison is performed by analysis of variance of repeated measurement data, and inter-group comparison is by multivariate analysis of variance (MANOVA). All statistical tests will be performed on both sides, and the difference will be considered statistically significant when *P* < 0.05.

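### Section 2.10 lets normality alone choose the Student t test although comparisons with control are 2:1; naming the Welch test outright would hold the error near 5% at almost no cost

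*Protocol article*

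**What the plan says.** All places are in the protocol article.

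- Section 2.10 announces two preliminary checks: "The homogeneity test of variance and normal distribution test will be adopted for measurement data".
- The same paragraph then fixes the method for continuous data. Of Student's method it says: "test will be used when the data obey the normal distribution, whereas the data not obeying the normal distribution will use rank sum test". Normality is the only condition named. No unequal-variance test appears, and nothing is said to follow from the homogeneity result.
- For repeated measurements, Section 2.10 names a different method: "inter-group comparison is by multivariate analysis of variance (MANOVA").
- Waist circumference, the primary outcome, is repeated data. Section 2.5.1 says "This index will be assessed on week 0, 2,4,6, 8, and 12".
- Section 2.7 randomises to the two moxibustion arms and "the lifestyle intervention (control group) in a 2:2:1 allocation ratio". Of the 135 evaluable participants, 54 are in each moxibustion arm, with "27 subjects in the lifestyle intervention (control group").

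Both comparisons with control (B v A and C v A) are therefore 2:1. C v B is 1:1.

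**The concern.** The Student t test, in its usual meaning, pools the two sample variances. With equal arms, pooling does little harm when the SDs differ. With 2:1 arms the pooled variance is weighted towards the larger arm, while the smaller arm contributes most to the true variance of the difference. The standard error is then too small if control is the more variable arm and too large if the treated arm is.

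Read literally, Section 2.10 sends normal data with unequal variances to the pooled test even after its own check has shown the inequality. At stake are the 5% error rate and the sensitivity of comparisons with control for any outcome on which the t test is used. Serum indices and blood pressure, measured only at weeks 0 and 8, are the likeliest; any single-visit or change comparison is also exposed.

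**Working it through.** **The plan's own figures.** Section 2.7 inflates for 10% dropout: 135/0.9 = 150, and by arm 54/0.9 = 60 and 27/0.9 = 30. These agree with the stated totals. The 135 itself cannot be re-derived, because the effect, SD and power sit in Table 2, which is not shown.

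**Inputs.** Arm sizes are 27 and 54 (Section 2.7), with two-sided 0.05 (Section 2.10). The ratio r = control SD / treated SD is an assumption, taken from 0.5 to 2, because no SD is readable. Data are normal, since that is when the rule selects the t test.

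**Why 2:1 matters.** Set the treated SD to 1.

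- Expected pooled variance = (26r² + 53)/79.
- Squared standard error used by the test = pooled variance × (1/27 + 1/54).
- True squared standard error = r²/27 + 1/54.

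At r = 2, the pooled variance is (104 + 53)/79 = 1.987 and the squared SE used is 1.987 × 0.0556 = 0.1104. The true value is 4/27 + 1/54 = 0.1667. The SE ratio is √(0.1104/0.1667) = 0.814, so the 1.96 cut-off behaves like 1.96 × 0.814 = 1.595, an error of about 11.1%.

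At r = 0.5, the pooled variance is (6.5 + 53)/79 = 0.753 and the squared SE used is 0.0418. The true value is 0.0278. The SE ratio is 1.227 and the effective cut-off is 2.406, an error of about 1.6%.

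**Simulated two-sided error, 27 v 54 (400,000 trials per row).** The gated column runs an F test of variances first and uses Welch if it rejects.

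| r | Pooled t | Gated | Welch | F test rejects |
|---|---|---|---|---|
| 0.5 | 1.7% | 4.9% | 5.0% | 98% |
| 0.67 | 2.6% | 4.4% | 4.9% | 63% |
| 0.8 | 3.5% | 4.2% | 5.0% | 23% |
| 1 | 5.0% | 5.0% | 5.0% | 5% |
| 1.25 | 6.9% | 6.0% | 5.0% | 27% |
| 1.5 | 8.5% | 5.8% | 5.0% | 68% |
| 2 | 11.1% | 5.1% | 5.0% | 98% |

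A Levene gate gives 4.3% to 6.2%. At 30 v 60 the results are nearly the same. At 54 v 54 (C v B) the pooled t stays between 4.9% and 5.1%, so that comparison is not affected.

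**Power.** The standardised effect is assumed to be 0.669, which gives the pooled test 80% at equal SDs. The average of the two variances is held fixed.

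| r | Pooled t | Gated | Welch |
|---|---|---|---|
| 0.5 | 76.7% | 87.9% | 88.0% |
| 0.8 | 78.8% | 80.5% | 82.7% |
| 1 | 80.1% | 80.0% | 79.5% |

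With a more variable treated arm, the pooled test gives up 82.7 − 78.8 = 3.9 points to Welch at r = 0.8, and 88.0 − 76.7 = 11.3 at r = 0.5. With the gate the loss is about 2 points or less. With equal SDs, Welch costs about 0.5 point. For r above 1 the pooled test shows more power than Welch, but only because its error exceeds 5%.

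**MANOVA.** A two-group MANOVA on five post-baseline visits at 27 v 54 (20,000 trials, assumed correlation 0.8, all SDs scaled by r) has error of 0.8% at r = 0.5, 5.1% at 1, 8.9% at 1.25, 13.1% at 1.5 and 20.3% at 2. Moving from the t test to MANOVA does not remove the dependence on equal spread.

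**The case against.** **The t test is not clearly the primary test.** This stands. Section 2.10 gives between-group comparison of repeated data to MANOVA, and on that wording waist circumference and most secondary outcomes fall there. A reader might infer that the false-positive rate or planned power of the primary comparison is wrong because of the t test. The article does not support that: Section 2.7 sizes the trial on waist circumference, and the t test is not clearly assigned to it.

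**Silence is not a decision to ignore the check.** The homogeneity test stands directly before the choice of tests, SPSS prints the unequal-variance result by default, and a condensed article may leave the fallback to a fuller plan. This stands in part. The gate is a fair reading, and under it most of the distortion goes, so 11.1% and 1.7% are outer bounds. What remains is that the written rule conditions on normality alone. A gate is also weakest where the inequality is moderate: at r = 1.25 the variance test rejects only about 24% to 27% of the time.

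**The plausible direction is the harmless one for error.** The natural mechanism, varied response to the added treatments in B and C, makes the treated SD larger. The pooled test is then conservative. This stands: a reader might infer inflated false positives, but the article gives no reason to expect a more variable control arm.

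**The power loss can be overstated.** Against a nominal 80% at fixed average variance, the pooled test falls short by about 3 points at r = 0.5 (80 − 76.7 = 3.3). The larger gap is to Welch, not to the planned power.

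**Conclusion.** The point holds as a low-cost improvement to the analysis wording. Where the t test is used for a 2:1 comparison with control, its two-sided error depends on the arms having equal SDs. For ratios from 0.5 to 2 it lies between about 1.7% and 11.1% if the homogeneity result is ignored, or about 4.2% and 6.0% if it gates the choice. Welch stays at about 5% throughout. If the treated SD is larger, the cost is lost power and not false positives.

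These figures rest on normal data, 54 v 27 evaluable, and SD ratios that are assumptions; no readable figure in the article shows unequal SDs. The same dependence applies to MANOVA and is larger there under the assumed visit correlation. That is a reason to protect the waist circumference comparison too, but it does not show that its planned power is wrong.

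**What to change.** In Section 2.10, name the Welch unequal-variance t test for all two-arm comparisons of continuous measures with control, and drop the homogeneity test as a step that selects the method. For the between-group comparison of waist circumference and other repeated outcomes, state that the analysis allows arm-specific variances or uses heteroscedasticity-robust standard errors.

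The t-test change is one sentence, uses output that SPSS already prints, and costs about 0.5 point of power if the SDs are equal. The change for repeated outcomes needs a further sentence naming the model. Both should be fixed before outcome data are seen.

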#### Diagnostic criteria

2.3.1

According to the criteria in the Comprehensive Medical Management Guidelines for Obese People jointly issued by the American Society of Clinical Endocrinologists (AACE) and the American College of Endocrinology (ACE) in May 2016:^[23]^ waist circumference (WC) ≥85 cm for male and 80 cm for female can be diagnosed as abdominal obesity.

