### Intervention

2.4

After baseline measurements, patients satisfying the inclusion criteria will be randomly divided into 1 of the 3 treatment groups, as shown below:

1.Group A: Lifestyle intervention.2.Group B: Moxibustion combined with lifestyle intervention.3.Group C: Moxibustion combined with characteristic lifestyle intervention of TCM.

All the participants will be instructed to return to visit the doctor every 2 week.

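### The named between-arm tests for waist circumference make no adjustment for the week-0 value, and a normality pre-test chooses between them

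*Protocol article*

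**What the plan says.** Section 2.5.1 states that "WC will be used as the primary outcome measure" and, of its timing, "This index will be assessed on week 0, 2,4,6, 8, and 12". Section 2.4 puts the baseline assessment ahead of allocation: "After baseline measurements, patients satisfying the inclusion criteria will be randomly divided into 1 of the 3 treatment groups". Week-0 WC is therefore a pre-randomisation value that should be on file for every participant.

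Section 2.10 calls for tests of normality and equal variance, then names Student's t: this "test will be used when the data obey the normal distribution, whereas the data not obeying the normal distribution will use rank sum test". For repeated measurements it prescribes repeated-measures ANOVA within groups, and adds that "inter-group comparison is by multivariate analysis of variance (MANOVA"). No covariate, ANCOVA or baseline-adjusted mixed model is named. Two things are left open: whether the t or rank-sum test is applied to follow-up values or to changes, and whether week 0 is one of the MANOVA responses.

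Section 2.8 describes simple randomisation in a 2:2:1 ratio, with no stratification named. Section 2.7 plans for 54, 54 and 27 evaluable participants, the 27 being the lifestyle-only controls (Group A).

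**The concern.** WC differs between people for reasons unrelated to treatment. Entry requires "waist circumference (WC) ≥85 cm for male and 80 cm for female", and no upper limit is set, so both sexes and a range of starting values will be present in each arm. Part of the spread in WC at follow-up is therefore already known at week 0. A comparison that ignores the week-0 value carries that spread in its standard error, and any chance difference in starting WC between arms passes into the estimate. Nothing in the allocation scheme balances starting WC, and the control arm is small.

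The normality pre-test adds a second problem. The trial's own data decide whether the result is a difference in means or a comparison of ranks, so the quantity estimated for the primary outcome is not fixed in advance.

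At stake is precision that would need no extra participants, in a trial whose Discussion lists its sample size as a limitation.

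**Working it through.** **Reproducing the plan's figure.** Section 2.7 gives 135 evaluable participants and 10% dropout: 135 / (1 − 0.10) = 150. By arm, 54 / 0.9 = 60 and 27 / 0.9 = 30. The stated total reproduces. The 135 itself cannot be recomputed, because effect size, SD and power are in Table 2, which is not shown.

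**Significance level.** Section 2.7 says "sample size required for each individual hypothesis testing was estimated at the 1-sided α level 0.025"; section 2.10 says "All statistical tests will be performed on both sides, and the difference will be considered statistically significant when" P is below 0.05. Both give a critical value of 1.96, so the difference in sidedness does not affect this point.

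**Chance baseline imbalance.** In units of the between-person SD, SE = √(1/n₁ + 1/n₂).

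- 54 v 27 (Group B or C against A): √(1/54 + 1/27) = 0.236. The 95% range is ±1.96 × 0.236 = ±0.46 SD, and the probability of exceeding 0.25 SD in either direction is 29%.
- 54 v 54 (C against B): √(2/54) = 0.192. The 95% range is ±0.38 SD, and the corresponding probability is 19%.

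**Variance of the between-arm difference.** Take equal SDs at both times, correlation r, and large samples. Relative to follow-up values alone (set to 1), change from baseline has variance 2(1 − r) and ANCOVA has 1 − r². ANCOVA therefore removes r² compared with follow-up values. Compared with change scores it removes 1 − (1 − r²)/[2(1 − r)] = (1 − r)/2.

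No r appears in the visible text, so every value below is an assumption.

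| r (assumed) | Change, 2(1 − r) | ANCOVA, 1 − r² | Removed v follow-up values | Removed v change |
|---|---|---|---|---|
| 0.3 | 1.40 | 0.91 | 9% | 35% |
| 0.5 | 1.00 | 0.75 | 25% | 25% |
| 0.7 | 0.60 | 0.51 | 49% | 15% |
| 0.8 | 0.40 | 0.36 | 64% | 10% |
| 0.9 | 0.20 | 0.19 | 81% | 5% |
| 0.95 | 0.10 | 0.098 | 90% | 2.5% |

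**How imbalance enters the estimate.** Given a baseline difference of Δ, a comparison of follow-up values shifts by rΔ and a comparison of changes by −(1 − r)Δ. For Δ equal to one SE (0.236 SD) and r = 0.7, the shifts are 0.7 × 0.236 = 0.165 SD and −0.3 × 0.236 = −0.071 SD. At r = 0.9 they are 0.212 SD and −0.024 SD. ANCOVA removes the shift in expectation.

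**The case against.** WC is measured six times, so the repeated-measurement clause may govern it rather than the t or rank-sum sentence, which concerns measurement data in general. If the MANOVA is read as group-by-time with week 0 among the responses, baseline is already used, roughly as in a change analysis. This is a fair point, and it limits the claim about size. It does not remove the point: no clause adjusts for baseline, and the text does not settle which reading applies. A MANOVA on follow-up visits alone would leave baseline unused. One that includes week 0 and reads the group main effect would dilute the contrast with a visit before any treatment.

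Four stronger readings are tempting, and the documents do not support them.

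- **Most of the precision is thrown away.** This needs follow-up values to be compared and r above 0.707. Neither is stated. Against change scores the saving never exceeds half for any r of zero or more. The entry cut-offs do not show that r is high; a lower limit truncates the range, which tends to reduce r.
- **Power would rise to 97% or more.** That follows only if 54 v 27 has 80% power on unadjusted follow-up values and r is at least 0.7. If the assumed 80% refers to change scores, ANCOVA gives 86%, 84% and 82% at r = 0.7, 0.8 and 0.9. The planned power and its basis are not visible.
- **Chance imbalance could match the treatment effect.** The expected effect is not visible. Taking 0.66 SD, the difference detectable with an assumed 80% power, an imbalance that large is 0.66 / 0.236 = 2.8 standard errors, with a two-sided probability of about 0.5%.
- **The unadjusted tests are invalid or biased.** Under randomisation they are not. Their standard errors already include baseline variation.

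**Conclusion.** The point holds as one of efficiency and conditional imbalance. The article itself fixes between-arm methods that leave out a baseline value it collects before randomisation, so this is a stated choice rather than a detail deferred to an unseen plan. The loss is 25% to 81% of the variance if follow-up values are compared, and 25% down to 5% if changes are compared, for r from 0.5 to 0.9. These ranges rest on assumed r, equal SDs over time and large-sample formulas. The imbalance figure of 0.236 SD rests only on the planned 54 and 27. Which range applies cannot be decided from the text. In large samples ANCOVA is no less precise than either alternative, so the recommendation is the same under both. The normality pre-test is a separate weakness in the same sentence and does not depend on r.

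**What to change.** In section 2.10, make the primary between-arm analysis of WC a linear model with arm as the factor and week-0 WC as a covariate. This can be ANCOVA at a named visit, or a mixed model over the post-baseline visits. Report adjusted mean differences with 95% confidence intervals. Use the same form for the other continuous outcomes that have a baseline value. Remove the rule that lets a normality test choose the primary method, and keep a rank-based comparison as a sensitivity analysis only. Sex and centre may be added as covariates, but the point does not require them.

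The cost is analysis wording, plus one degree of freedom for the covariate, which is negligible with 54 + 27 = 81 participants in the smaller comparisons. No new data, visits or participants are needed.
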